## **7. target number of patients and duration of clinical study**

### **7.1. target number of cases**

Overall clinical research: Number of participating facilities: 7, Target number of cases: 20

| Name of medical institution                      | Target number of cases |
|--------------------------------------------------|------------------------|
| Hiroshima University                             | 3                      |
| Kanazawa University                              | 4                      |
| Osaka University                                 | 3                      |
| Nihon University                                 | 3                      |
| National Center for Child Health and Development | 3                      |
| St. Marianna Medical University                  | 2                      |
| Showa University Hospital                        | 2                      |

### **7.2. duration of clinical research**

Registration period jRCT first publication date - March 31, 2024

Period of the study jRCT first publication date - March 31, 2026 (from registration of the implementation plan in the Japan Registry of Clinical trials (jRCT) to registration of the summary report summary in the jRCT)

## **8. evaluation and reporting of adverse events (e.g., illness)**

### **8.1 Definition of Adverse Events (Diseases, etc.)**

Adverse Event (Disease, etc.) means all unwanted or unintended injuries or illnesses or signs thereof (including abnormal laboratory values) that occur in a Research Subject, regardless of whether or not they are causally related to the clinical research conducted. (2) "Unintended injury or disease" means any unfavorable or unintended injury or disease or its symptoms (including abnormalities in clinical laboratory values) that occurs in research subjects, whether or not there is a causal relationship with the clinical research conducted. In this clinical research, all undesirable or unintended injuries or illnesses, or signs thereof (including abnormal laboratory values) that occur in research subjects after the administration of Kesuyu Kashuyu is started shall be considered as adverse events. Adverse Events.

---

Serious adverse event" means an adverse event that falls under any of the following categories

1) Deadly

2) May lead to death

3) Admission to a medical institution for treatment or prolonged hospitalization is required

4) Obstacles

5) May lead to impairment

6) Congenital diseases or anomalies in later generations

The term "unanticipated serious adverse event" means a serious adverse event that is not described in the research protocol, informed consent document, etc. or, even if described, the nature or severity of the event is not consistent with the description.

An adverse drug reaction (ADR: adverse drug reaction) is an adverse event for which a causal relationship to the use of the drug in question cannot be denied (including those for which the causal relationship is unknown).

## **8.2. evaluation and reporting of adverse events**

In this clinical study, adverse events and side effects will be evaluated using CTCAE v4.0-JCOG, with adverse events listed and graded. Grading of adverse events will be based on the closest definition of Grade 1 to 4, respectively. If a specific treatment is listed in the Grade, it should be graded based on its clinical necessity. In this study, an adverse event is judged as a Grade worsening by one or more levels in CTCAEv4.0. Abnormal laboratory values are also graded in the same way. Adverse events that occurred prior to treatment with the study drug will also be reported as adverse events if the Grade worsens by one or more levels.

Severity of adverse events

The severity of the adverse event shall be one of the following

1. non-serious

2. serious

Causality Classification

The causal relationship to the study drug and protocol treatment will be determined by one of the following categories, respectively

1. causality cannot be ruled out: there is a reasonable causal relationship with the study drug or protocol treatment (including cases where causality is unknown due to insufficient information)

2. causality can be ruled out: there is no reasonable causal relationship to the study drug or protocol treatment.

Adverse Event Outcomes

Adverse event outcomes shall be classified as one of the following categories.

1. recovery: adverse event returned to Grade 0 in CTCAE v4.0 or Grade prior to study drug administration

- 
2. minor: adverse event returned to Grade 1 in CTCAE v4.0 (applies to AEs Grade 2 or higher)
  3. unrecovered: Adverse event has not resolved and is in the same Grade as when the adverse event occurred.
  4. recovered but with sequelae: adverse events resolved but with sequelae
  5. death: The research subject has died
  6. unknown: no information, unknown outcome

#### Response to adverse events

When an adverse event occurs in a research subject, the principal investigator and the research assistant investigator will first ensure the treatment and safety of the research subject and take appropriate measures. The observation period for adverse events in this clinical research will be from the start of protocol treatment until 4 weeks after the protocol treatment is completed or discontinued, and follow-up observation will be conducted thereafter until recovery as much as possible. However, this does not apply to cases in which symptoms that develop due to worsening of the primary disease or complications of the research subject have become chronic, or in cases in which continuous observation is difficult due to transfer to a different hospital or start of post-treatment.

The principal investigator and the research assistant investigator will make the following evaluations of the adverse events that occur and document them in the case report form. If more than one adverse event occurs, the adverse event should be judged separately.

1. identification of suspect drug
2. severity and severity of adverse events that occurred
3. existence of a causal relationship with the study drug
4. predictability

When a serious adverse event is recognized, the principal investigator shall promptly report it to the head of the institution in accordance with the institution's procedures, as well as to the principal investigators at other institutions.

Once a year, the principal investigator reports the progress of the clinical research and the occurrence of adverse events associated with the implementation of the clinical research to the Accredited Clinical Research Review Committee and the administrator of the medical institution where the clinical research is conducted.

### **8.3. anticipated adverse events**

Serious Side Effects of Kesuyu Kashuyu

- 1) Pseudohyperaldosteronism: frequency unknown
- 2) Myopathy: frequency unknown

### **8.4. reporting and handling of serious adverse events**

The Principal Investigator will make arrangements, including a contract/memorandum of understanding (MOU), with the study drug provider, Tsumura Corporation, prior to the start of the

study regarding adverse event reporting procedures and reporting details. Communication with the principal investigator and other relevant personnel at each research institution will be in accordance with the attached "Procedures for handling illnesses and other incidents in clinical research to evaluate the efficacy of Eppikajutsuto for lymphatic malformations".

**8.4.1. report of serious adverse events occurring in the conduct of the clinical research (including serious adverse events resulting from malfunctions )**

Reports should be made in accordance with the "Procedures for Reporting Diseases and Malfunctions in Clinical Research under the Clinical Research Act" or other similar procedures at each site.

- 1) In the event of a serious adverse event (including serious adverse events that may occur due to malfunction), the research physician shall take appropriate measures and immediately report to the principal investigator, regardless of the causal relationship to the study drug.
- 2) The investigator shall promptly determine whether or not the serious adverse event has a causal relationship to the conduct of the clinical research and whether or not it is a known event, and respond to it in accordance with the "Procedures for Reporting Diseases and Defects in Clinical Research under the Clinical Research Act at Kanazawa University". That is, in the event of a serious adverse event, a "Report of Disease, etc. (First Report) (Uniform Form 8)" (and a "Report of Disease, etc. (Pharmaceuticals)" (Appendix Form 2-1) in the case of a serious adverse event requiring a report to the Minister of Health, Labor and Welfare) shall be filed and reported to the hospital director within 72 hours from the time of knowledge (for events that have a suspected causal relationship with the relevant clinical research). (The secretariat of the Accredited Clinical Research Review Committee will also be submitted for events that are suspected to have a causal relationship with the clinical research in question).
- 3) The Research Office will report the details reported in 2) above to the administrator of Kanazawa University Hospital, the Principal Investigator, other investigators, and the manufacturer and distributor of the study drug, as well as to the Effectiveness and Safety Evaluation Committee as necessary.
- 4) Other principal investigators report to the administrator of the medical institution to which they belong.
- 5) The administrator of the site will take necessary measures for the adverse event.
- 6) The secretariat of the Accredited Clinical Research Review Committee shall report the opinions of the Accredited Clinical Research Review Committee to the Research Office, which in turn shall report the contents of the report to the administrator of Kanazawa University Hospital, the principal investigator, the principal investigator and the manufacturer and seller of the study drug.

---

7) Details of further procedures regarding adverse events will be in accordance with the serious adverse event procedures established by each institution.

<Contact information in case of emergency

Center for Chinese Medicine, Hiroshima University Hospital

Address: [name]

[contact]

[contact]

#### **8.4.2. report to the Minister of Health, Labor and Welfare, etc.**

In the event of an unanticipated serious adverse event suspected to have resulted from the conduct of said clinical research, the investigator shall submit a "Report on Disease (Pharmaceuticals)" (Appendix Form 2-1) to the Minister of Health, Labour and Welfare within 7 days of learning of the occurrence regarding death or the threat of death, and within 15 days otherwise.

#### **8.4.3 Detailed and additional reports**

For serious adverse events reported to an accredited clinical research review committee, the investigator shall submit a "Report of Drug Disease, etc." (and a follow-up report of the "Report of Disease, etc." if necessary) to the accredited clinical research review committee.

If the outcome of such adverse event is "unrecovered" or "unknown," the patient should be followed up as much as possible.

### **9. endpoint definition**

#### **9.1. main endpoints**

Primary Endpoint: Tumor response assessed by MRI-based volumetric analysis at 6 months, defined as at least a 20% reduction in volume. For diffuse lesions, reduction in the primary lesion size will be assessed.

Rationale: Based on past case series, a measurable degree of shrinkage is expected at 6 months of drug administration.

Prior to lesion evaluation, a definitive diagnosis is made by the imaging evaluation committee to determine efficacy.

Methods of measuring lesions

1. MRI is performed.

Required imaging methods:

T1WI; T1-weighted image, T2WI; T2-weighted image, T2FS; T2 fat suppressed image, 3D-T2FS; 3D-T2 fat suppressed image. In all cases, axial sectioning is mandatory.

Gd-T1FS; post-contrast T1 fat suppression images are not required and may be taken only when necessary for differential diagnosis.

T2 fat-suppressed images should be taken in gapless mode. The basic slice thickness is 3-5 mm, but if the lesion is large, 6-8 mm is acceptable.

Definitive evaluation is based on volume comparison, using 3D-T2FS, or if 3D-T2FS is not available, T2FS with gapless imaging.

## 2. evaluation method

Two evaluators (Imaging Evaluation Committee: Diagnostic Radiologist) who meet the following criteria

(1) be an external evaluator, and (2) be a central diagnosis rather than a facility-by-facility evaluation.

OsiriX, a DICOM viewer, shall be used for measurement.

Before evaluation, the evaluators confirm the extent of the lesion to be evaluated in two or more directions, such as axial and coronal sections, and establish the appropriate measurement area. As a rule, the volume is measured using the axial section image.

For the measurement, two evaluators shall independently measure the volume. The measured values shall be rounded off to two decimal places. The average of the two evaluators' final evaluation values shall be the final evaluation value. The inter-observer correlation coefficient (ICC) is calculated to evaluate the reproducibility of the measurement values among the evaluators.

If the respective values differ by more than 10%, it is desirable to confirm the ranges measured by each other, since the ranges and sites to be evaluated may be very different.

After the measurement, all the area and ROI information measured in each slice should be saved as the original data of the measured values. Specifically, the data should be saved in a movie, JPEG image, or other format that separates the evaluation period for each patient, and submitted to the secretariat together with the data of the definitive evaluation value.

The primary evaluation is a comparison of pre-treatment and 6 months post-treatment.

## 3. measurement area

The volume of the lymphatic malformation lesion will be measured objectively for the target lesion determined at the start of the study.

## 9.2. secondary endpoints

1. percentage decrease of more than 50% of volume

2. lesion reduction rate

3. 10% improvement in quality of life associated with treatment

4. safety of administration of koshuizhuyuu

5. adherence to the administration of Koshuizhuyuu (percentage of patients who were able to take

---

at least 70% of their medications)

Rationale: 3) Even if there is no marked change in size, QOL and symptom improvement has been reported, so it was set as a secondary endpoint; 4) Pseudohyperaldosteronism is known to be a major side effect of Eppikajutsuto, but its occurrence in children is not well reported.

## **10. statistical considerations**

### **10.1 Basis for Setting Target Number of Cases**

In our retrospective case series study, the response rate (20% volume reduction at 6 months) to treatment with Eppikajutsuto in LM patients was 83% (in submission). Conservatively taking into account the overestimation tendency of the retrospective study design of prior reports, we expect a response rate of at least 50% with this treatment in the study's patient population. In the same study, none of the patients had a response to no treatment, and both patients had an increasing trend. Considering the exploratory nature of this study, the first prospective clinical trial, the number of patients will be designed based on accuracy. The lower limit of the two-sided 90% confidence interval (corresponding to a one-sided significance level of 5%) is 29.1% (the upper limit is 70.8%) if 9 patients respond (response rate of 50%) in the 18 patients in the analysis.

Considering that the main purpose of this exploratory study is to collect information that can be used for the next phase of the study, we believe that 18 cases is an appropriate number of cases. Since the number of patients seen annually at each site is approximately 5 cases each, it is possible to enroll the target number of cases in 3 years.

Based on the above considerations, the target number of cases was set at 20 to ensure accuracy in case a few cases were excluded from the analysis.

#### **10.1.1 Reestablishment of target number of cases**

As mentioned in 10.1, considering the rarity of the subject cases in this study, we believe that the number of cases of 20 is close to the upper limit from the viewpoint of feasibility. On the other hand, considering that the main purpose of this study is to collect information that can be used for the next phase, although it is positioned as an exploratory study, the collection of exploratory data that contributes to the identification of subpopulations with higher potential for efficacy is one of its important objectives, and a larger number of cases would be preferable as long as feasibility permits.

Based on the above considerations, if it becomes clear during the study period that the target number of 20 cases can be enrolled earlier than previously expected, the target number of cases will be considered for re-setting according to the progress at that point in time. From the viewpoint of feasibility, we currently plan to slightly increase the target number of patients at that time as well. However, we will consider re-setting the target number of patients appropriately according to the information that is updated and accumulated both inside and outside the study up to that point.

## **10.2. population to be analyzed**

The primary analysis of the primary and secondary endpoints will be performed on the Full Analysis Set (FAS). Analysis will also be performed on the Per Protocol Set (PPS) and compared with the FAS to confirm the stability and sensitivity of the analysis results.

The FAS is defined as a population that excludes from all enrolled cases any case that falls into one of the following categories: (1) cases with a confirmed diagnosis of a disease that is not eligible, (2) cases that violate important exclusion criteria, (3) cases that have never received protocol treatment since enrollment, or (4) cases with no data at all since enrollment.

The PPS will be defined as patients who meet the minimum requirements for key variables in the study protocol, for whom protocol treatment was not possible or was discontinued, but who have completed MRI evaluation and have no serious protocol violations regarding eligibility criteria, concomitant prohibited drugs, etc. The Safety Analysis Set (SAS) is defined as all enrolled patients, excluding those who have never received protocol treatment since enrollment.

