## 1. purpose

To evaluate the efficacy, dose-response, and safety of Eppikajutsuto in patients with lymphangitic malformations (LM) in an open-label, pre- and post-administration study. The primary endpoint will be response from baseline in tumor volume by volumetry. Secondary endpoints will be 1. 50% or greater volume reduction, 2. shrinkage rate, 3. 10% improvement in quality of life, 4. safety, and 5. adherence to medications.

---

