#### **5.6. discontinuation of protocol treatment**

The investigator or subinvestigator will discontinue the study drug if the investigator or subinvestigator determines that continuation of protocol treatment is not feasible for any of the following reasons. The date, reason, and progress of discontinuation will be documented in the medical record and the case report form (CRF), and necessary tests will be performed at the time of discontinuation or dropout to evaluate efficacy and safety.

If the drug is discontinued due to the occurrence of an adverse event, the patient should be followed up as much as possible until the current status is restored.

(1) When a research subject or a surrogate withdraws from participation in clinical research or withdraws his/her consent.

(2) When it is found that eligibility is not satisfied after registration

(iii) When the underlying disease is completely cured and there is no longer a need for continued administration

(iv) When it is determined that continued administration of the test drug is not desirable due to worsening of the underlying disease

(5) When it is difficult to continue the clinical research due to exacerbation of complications

(6) When it is difficult to continue the clinical research due to adverse events

(vii) In case of significant non-adherence (when it is determined that less than 70% of the total scheduled doses will be taken or more than 120% of the total scheduled doses will be taken)

(viii) If the research subject does not come to the hospital due to relocation, etc.

(ix) When the entire clinical research is discontinued

(10) When the principal investigator determines that it is appropriate to discontinue the clinical research for other reasons

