#### **2. shrinkage rate**

---

For each case, determine the percentage reduction in volume of lymphatic malformations by volumetry at 6 months of drug administration from before the start of drug administration.

3. 10% improvement in QOL

Use EQ-5D-5L Japanese version for Japan.

Depending on the respondents' understanding of the questionnaire, Effective\_Japan (Japanese) EQ-5D-5L Paper Self-Complete v1.2 or Effective\_Japan (Japanese) EQ-5D-5L Paper Proxy2 v1.1 is used to determine the percentage of improvement in quality of life by 10% or more.

4. safety

For adverse events, determine the type and frequency along with a list. If necessary, use an accurate method based on a binomial distribution when determining confidence intervals .

5. medication adherence

Obtain numerical values for medication adherence. If necessary, use an exact method based on a binomial distribution when determining confidence intervals.

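### Section 10.2 places every secondary endpoint, and so literally safety, on the FAS, while the Safety Analysis Set it defines is given no analysis

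*Protocol*

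**What the plan says.** Section 10.2 sets one rule for all endpoints: "The primary analysis of the primary and secondary endpoints will be performed on the Full Analysis Set (FAS". It names one further population for comparison: "Analysis will also be performed on the Per Protocol Set (PPS) and compared with the FAS".

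Safety is among the secondary endpoints. Section 1 lists "4. safety, and 5. adherence to medications", and section 9.2 lists "4. safety of administration of koshuizhuyuu". The analysis of safety is item 4 under the secondary endpoint methods in section 10.3.3: "For adverse events, determine the type and frequency along with a list". That item names no population.

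Among the cases that section 10.2 removes from the FAS are "1) cases with a confirmed diagnosis of a disease that is not eligible, (2) cases that violate important exclusion criteria". Two further categories are cases never treated and cases with no data after enrolment. The section then adds: "The Safety Analysis Set (SAS) is defined as all enrolled patients, excluding those who have never received protocol treatment since enrollment". No sentence says which analysis uses this set, and the term does not appear elsewhere in the protocol at hand.

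Section 5.6 lists as a reason for stopping the study drug: "2) When it is found that eligibility is not satisfied after registration".

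**The concern.** A safety analysis normally counts everyone exposed. The SAS does that. The FAS does not, because two of its exclusions depend on diagnosis and eligibility and take no account of whether the child took the drug. The only population rule that reaches the safety endpoint is the FAS rule.

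The children on whom the two sets differ may not be a neutral subset. The exclusion criteria in section 3.2 include a past allergic reaction to the drug and serious disease other than lymphatic malformation, and the rationale given there for these criteria includes safety. If they count as important, which the protocol does not define, the FAS removes exposed children whom the protocol itself treats as a safety concern.

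The stake is an understated adverse event frequency in a trial of about 20 children. Section 9.2 says that the main known side effect is poorly documented in children, section 8.3 gives its frequency as unknown, and section 10.1 says that the main purpose is to inform the next phase.

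**Working it through.** **Step 1. The two sets compared for dosed children (section 10.2).** Children never dosed are outside both sets.

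| Dosed child | FAS | SAS |
|---|---|---|
| Eligible, with data | in | in |
| Confirmed ineligible disease | out | in |
| Violates an important exclusion criterion | out | in |
| Fails only a selection criterion, such as the weight limit in 3.1 | not clearly removed | in |
| No data at all after enrolment | out | in, but with no events to count |

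Rows 2 and 3 carry the point.

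**Step 2. Can a dosed child fall into rows 2 or 3?** Section 5.3.4 starts dosing straight after enrolment. Section 9.1 has the imaging committee make the definitive diagnosis before lesions are evaluated, but does not fix its timing relative to the first dose. Section 5.6 foresees ineligibility that comes to light after registration. Such a child is a realistic case, though the protocol gives no expected number.

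**Step 3. Check of the interval method on the plan's own figure.** Section 10.1 gives a two-sided 90% interval of 29.1% to 70.8% for 9 of 18 responders. The Clopper-Pearson interval uses beta quantiles: lower = B(0.05; x, n−x+1), upper = B(0.95; x+1, n−x). With x = 9 and n = 18 it gives 29.12% to 70.88%. This reproduces the stated interval; its upper limit is truncated rather than rounded.

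**Step 4. Illustration of size.** Inputs:
- 20 enrolled and 18 analysed (section 10.1).
- Exact binomial intervals where intervals are needed for safety (10.3.3 item 4), at the default two-sided 90% level (10.3.5).
- Assumptions: all 20 children are dosed, and both of those outside the 18 are dosed children whom the FAS removes.

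*No events.* The upper limit of the two-sided 90% interval, which is the one-sided 95% limit, is 1 − 0.05^(1/n):
- FAS, n = 18: 1 − 0.05^(1/18) = 15.3%
- One child excluded, n = 19: 1 − 0.05^(1/19) = 14.6%
- SAS, n = 20: 1 − 0.05^(1/20) = 13.9%

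*One event, in an excluded child.*
- FAS: 0/18 = 0%, upper limit 15.3%
- SAS: 1/20 = 5%, exact 90% CI 0.3% to 21.6%

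*Two events, one in each excluded child (the extreme under this assumption).*
- FAS: 0/18 = 0%, upper limit 15.3%
- SAS: 2/20 = 10%, exact 90% CI 1.8% to 28.3%

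The smaller denominator alone moves the limit by 15.3 − 13.9 = 1.4 percentage points. The omission of an event changes the result from never seen to seen.

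**The case against.** The strongest reply is that the intent is plain. A set called the Safety Analysis Set, defined in the same section and keeping every dosed patient, has no other plausible use, and a comparison of FAS with PPS fits efficacy more naturally than adverse events. This largely stands: the defect is probably a drafting slip. It does not remove the conflict, because the express sentence covers all secondary endpoints without exception.

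A second reply is that the matching of endpoints to populations can wait for the statistical analysis plan, which is not at hand. That would answer a complaint that 10.3.3 names no population. It does not answer this point, because the protocol makes a positive assignment, and an analysis plan that used the SAS for safety would contradict it.

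Third, a reader might infer that adverse events in these children would be lost. The documents do not support that. Section 8.2 has events observed from the start of treatment until 4 weeks after its end and documented in the case report form, and section 8.4.1 has serious events reported whatever their cause. Neither depends on an analysis set. What is affected is the summary frequency and its denominator.

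Fourth, the group is small. The registration centre verifies eligibility before treatment begins (section 4.1). Not every ineligible child leaves the FAS, and a child with no data contributes no events in either set. All of this stands and limits the size of the point.

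**Conclusion.** The point holds as an internal inconsistency in section 10.2. As written, the safety endpoint falls under the FAS rule, and the set designed for safety has no stated use. A reader might go further and conclude that the trial will in fact drop all ineligible children from its safety results. The text does not support that: the name of the SAS suggests the opposite intent, and only a confirmed ineligible disease or an important exclusion violation clearly removes a child who has data.

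The size is unknown, because the protocol does not say how many dosed children might be excluded. The figure of 2 in 20 is an assumption drawn from the gap between 20 and 18 in section 10.1, and that gap could equally be filled by children never dosed, whom both sets omit. Under the assumption, the effect with no events is minor (15.3% against 13.9%). If an excluded child had the only event, the summary would read 0/18 where the exposed population shows 1/20. In so small a trial, that possibility justifies settling the wording before analysis.

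**What to change.** In section 10.2, limit the FAS and PPS sentences to efficacy and adherence and give the SAS its role, for instance: *The primary endpoint and secondary endpoints 1, 2, 3 and 5 are analysed on the FAS, with the PPS for comparison; secondary endpoint 4 (safety) is analysed on the SAS.* In section 10.3.3 item 4, add that adverse event types, frequencies and any confidence intervals are based on the SAS.

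The cost is two sentences, with the approval that section 15.2 requires for a protocol revision. Sample size, data collection, visits and treatment do not change. Section 10.5 requires changes to the statistical analysis plan to precede the analyses they affect, and this wording should be settled by the same point.

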### 5.3.5 Dose and Schedule Change Criteria

Postponement: not administering at the prescribed date and time, but delaying it.

Postponements may be taken after a meal or at a later time if the dose is not taken at the predetermined time due to forgetting to take it or for other reasons.

Discontinuation: permanent and continuous withdrawal of the entire treatment or a specific drug.

---

It is assumed that the drug will not be restarted.

Keep a record of the patient's medication intake and monitor the patient's medication status. If adherence is poor and the patient is unable to take the medication, discontinue the medication. In such a case, continue to monitor the patient.

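### The adherence endpoint is analysed on the FAS, which drops any child who was given the drug but never took a dose, so adherence can be overstated if such children occur

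*Protocol*

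**What the plan says.** Section 9.2 item 5 defines the endpoint as "adherence to the administration of Koshuizhuyuu (percentage of patients who were able to take" "at least 70% of their medications" (the product name is a translation variant of the study drug). The denominator is given only as patients.

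Section 10.2 assigns the population: "The primary analysis of the primary and secondary endpoints will be performed on the Full Analysis Set (FAS", with the Per Protocol Set (PPS) as a comparison. Two of the four FAS exclusions matter here: "3) cases that have never received protocol treatment since enrollment, or (4) cases with no data at all since enrollment".

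Section 10.3.3 item 5 says only "Obtain numerical values for medication adherence", with an exact binomial interval if one is needed. It names no other population. The safety set in 10.2 also leaves out the never-treated. The PPS is supportive only and requires a completed MRI evaluation, so it is not built to keep them.

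Section 5.3.5 deals with children who have difficulty once on treatment: "If adherence is poor and the patient is unable to take the medication, discontinue the medication". They continue to be observed.

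**The concern.** The endpoint asks whether a child can take the drug. FAS rule (3) selects children partly on the answer, because a child with zero intake leaves the denominator when that child should count as a failure. Leaving out never-dosed children is a reasonable choice for the volume response. It fits poorly with an endpoint about ability to take the medication.

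The use of the figure makes this worth settling. Sections 10.1 and 10.1.1 give the main purpose as informing the next phase. The children weigh 25 kg or less and take an oral extract three times a day for 6 months. A reader of the adherence percentage will want to know whether such children can manage that, and nothing in the protocol says the figure is conditional on having started.

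This is not a detail left to a statistical analysis plan. The protocol states a population for this endpoint.

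**Working it through.** **The plan's own figure.** The only precision statement is in 10.1, for the response rate: the lower limit "is 29.1% (the upper limit is 70.8%) if 9 patients respond (response rate of 50%) in the 18 patients in the analysis". A two-sided 90% Clopper-Pearson interval for 9/18 gives 29.12% to 70.88%. This reproduces the stated limits, with the upper one truncated rather than rounded. The same method is used below. No precision is stated for adherence.

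**Inputs.**
- N = 20, the target number of cases (7.1 and 10.1). It is taken here as the number of eligible children to whom drug was dispensed.
- x = number of children reaching 70%. Assumed; not in the protocol.
- k = number of children given the drug who never took a dose. Assumed; not in the protocol, so a range is shown.

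**Formula.** The FAS rate is x/(N − k). The rate that counts never-dosed children as failures is x/N. The difference is

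x/(N − k) − x/N = [x/(N − k)] × k/N,

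that is, the FAS rate times k/N. It cannot be negative. Since the FAS rate is at most 100%, it is at most k/20, or 5 points per child.

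**Results with x = 14 held fixed (90% exact intervals).**

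| k | FAS | Never-dosed counted, N = 20 | Difference (points) | Largest possible (points) |
|---|---|---|---|---|
| 0 | 14/20 = 70.0% (49.2 to 86.0) | 70.0% (49.2 to 86.0) | 0 | 0 |
| 1 | 14/19 = 73.7% (52.4 to 89.0) | 70.0% (49.2 to 86.0) | 3.7 | 5 |
| 2 | 14/18 = 77.8% (56.1 to 92.0) | 70.0% (49.2 to 86.0) | 7.8 | 10 |
| 3 | 14/17 = 82.4% (60.4 to 95.0) | 70.0% (49.2 to 86.0) | 12.4 | 15 |

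With better adherence and k = 2, 16/18 = 88.9% (69.0 to 98.0) becomes 16/20 = 80.0% (59.9 to 92.9), a difference of 8.9 points.

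For scale, the interval around 14/20 is 86.0 − 49.2 = 36.8 points wide. The shift from one child is small beside sampling error, but it always runs the same way.

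**Which children are affected.**

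| Child | In the FAS? | Adherence status |
|---|---|---|
| Starts, then takes under 70% or is stopped for poor adherence | Yes; no rule removes the child for this | Counted as below 70% if intake is recorded |
| Given the drug, refuses every dose | No, rule (3) | Known failure, not counted |
| Family withdraws before drug is dispensed | No, rule (3) | Says nothing about ability to take the drug |
| Found to have an ineligible disease or to violate an important exclusion criterion | No, rules (1) and (2) | Not relevant to the target population |
| No data at all since enrollment | No, rule (4) | Unknown |

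Only the second row is a clear error for this endpoint.

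**The case against.** Four arguments on the other side have weight.

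**The bias is conditional.** A reader might infer that the adherence figure is overstated as it stands. The protocol does not support that. It gives no expected number of never-dosed children, and section 5.3.4 starts dosing immediately after enrollment, so the gap in which a child can be enrolled but never dosed is short. This stands, and the point is worded accordingly.

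**Most non-adherers stay in.** A reader might take 5.3.5, or the below-70% discontinuation reason in 5.6, as evidence that the children the protocol expects to fail are the ones removed. They are not. Those sections mainly concern children who are already on treatment, and no FAS rule removes them for poor adherence. This also stands.

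**Not every excluded child is a failure.** It is tempting to say that the excluded children can only be failures. That holds for a child who was given the drug and took none. It does not hold for families who withdrew, for ineligible children, or for children without data. Nor can the allowance in 10.1 be read as two refusers: "the target number of cases was set at 20 to ensure accuracy in case a few cases were excluded from the analysis" covers exclusion for any reason.

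**Adherence among starters is a legitimate quantity.** It is, but 9.2 says only patients, so the reader is not told that this is what is reported. One could also argue that a child counts as treated once the drug is dispensed. Section 5.3.4 describes the treatment as oral administration, so taking a dose is the more natural reading. If the sponsor means dispensing, the text should say so.

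**Conclusion.** The concern holds as a minor point. FAS rule (3) takes a known adherence failure out of the denominator of the adherence endpoint, and no other stated rule puts it back. The effect can only raise the percentage or leave it unchanged. It is at most 5 points per affected child when 20 children are in the denominator, and zero when there are none.

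This rests on three assumptions: never having received treatment means never having taken a dose; all 20 children are eligible and were dispensed drug; and the number of refusers is unknown, so the range of 0 to 3 is illustrative. With fewer children dispensed drug, the maximum per child rises slightly (1/18 = 5.6 points at 18).

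The one-way direction applies to dispensed-but-never-dosed children only. The net effect of all four FAS exclusions against all enrolled children has no fixed sign, because rules (1) and (2) act regardless of adherence. The primary endpoint is not touched, and adherence has no success threshold.

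**What to change.** In 10.2 and 10.3.3 item 5:

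- Analyse adherence on eligible enrolled children to whom study drug was dispensed, and count those who never took a dose as not reaching 70%.
- Leave out families who withdrew before dispensing and children found ineligible.
- Report the number of never-dosed children and the number with no data.
- As a sensitivity analysis, show children with no data both ways, as reaching and as not reaching 70%. Note this as an exception to 10.3.6, which otherwise rules out filling in missing values.
- Keep the FAS figure as supportive.

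The cost is a sentence or two in 10.2 and 10.3.3 and a cross-reference in 10.3.6. No new data are needed, because 5.3.5 already requires intake records and 5.7 already has the drug custodian manage disbursement. The only downside is a possibly slightly less favourable adherence figure.
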